#### A) True auriculotherapy using pressure with vaccaria seeds (TAP)

Application of auricular implants with vaccaria seeds (vaccaria segetalis Garcke, known in China as Wang bu liu xing) as an individualized form of sensory stimulation, affixed to the auricular pavilion by means of flesh-coloured sticking plaster. Selection of the auricular points will be made in accordance with the pain characteristics and the sensitivity of the auricular zones, examined using a 250 gr pressure detector [[26], 29]. The patients will be requested to squeeze the implant with their finger 10 times, 3 times a day. These implants will remain in place for one week.

#### B) Placebo auriculotherapy (PAP)

The same protocol will be followed, under the same conditions as for TAP, but with the application of sticking plaster over inactive black plastic discs, with a diameter of 1.5 mm, simulating the appearance of the auricular implants used in the TAP.

Any adverse reactions or side effects that may occur will be recorded in the corresponding data logbook, stating details of the reaction, and date of occurrence.

The same time should be dedicated to the patients in each of the groups, as should that employed in the pre and post-session evaluations (Fig. 1).

**Figure 1 F1:**
[figure not shown]
**Flow diagram for the study**. Work scheme with description of assessment visits and times.

### Results measures

Each patient will fill in a self-response questionnaire before beginning the treatment (T0), at one week after ending treatment (T1) and after six months (T2). This questionnaire will include one-dimensional data (100 mm visual analogue scale) and multidimensional data (McGill Pain Questionnaire, Spanish version [30]) on rachialgia, medication currently being taken and health-related quality of life (SF-12), together with information on days off work due to rachialgia. Additionally, before beginning treatment, the patients will be asked to fill in a form on sociodemographic questions. Any adverse effects of the study techniques, and any use of rescue medication by the patient will also be recorded. During the initial evaluation, an anamnesis will be obtained on the characteristics of the rachialgia, and note will be taken of the duration of the pain. In each treatment session, the therapist will record the five pain-related variables that constitute the Lattinen test (LT), which is widely used in pain treatment clinics in Spain [31]. These variables are: pain intensity, pain frequency, consumption of analgesics, level of activity, and nocturnal hours' sleep. Each item is scored on a Likert scale from 0 to 4; thus, the sum of the five variables may range from 0 to 20 points, with higher scores reflecting greater pain severity. In addition, the auricular points selected for each patient will be recorded (Table 1).

**Table 1 T1:** Data collection schedule. Measurement times and variables used in the study.

Visit No.	T0	Weekly treatment								T1	T2
Week No.	0	1	2	3	4	5	6	7	8	9	24
Data provided by the patient											
Pain intensity (VAS 100 mm)	X									X	X
Multidimensional pain evaluation (MPQ-SV)	X									X	X
Quality of life (SF-12)	X									X	X
Analgesics and antiinflammatory drugs prescribed	X									X	X
Sociodemographic variables	X										
Credibility and expectations				X							
Improvement perceived by the patient										X	
Assessment of blinding effectiveness										X	
Data provided by the therapist											
Multidimensional pain evaluation (LT)	X	X	X	X	X	X	X	X	X	X	X
Auricular points used		X	X	X	X	X	X	X	X	X	
Adverse events		X	X	X	X	X	X	X	X	X	
Economic evaluation											
Direct and indirect costs: healthcare professionals and patients	X									X	X

VAS 100 mm: Visual analogue scale (0–100 mm); MPQ-SV: McGill Pain Questionnaire, Spanish version; LT: Lattinen test

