### Randomization and treatment allocation

Sampling will be by consecutive selection in accordance with the inclusion-exclusion criteria, for a period of 12 months until the sample is complete. The randomized allocation to each of the two branches of the study will be carried out using specialized computer software (Epidat v. 3.1), at the Research Unit of the Costa del Sol Hospital (Málaga, Spain), in a 1:1 plan (true auricular pressure: placebo) in blocks of 6, stratified by therapist. Neither the clinics nor the healthcare professional participating in the study will be involved in the randomization process, and the randomization sequence will remain concealed until the end of the study. Patients who meet the criteria for inclusion and who sign their informed consent will be included in the study. After inclusion in the study, the healthcare professional will call the randomization clinic at which the patient is registered, and will be informed, both by phone and by fax, which of the two study branches the patient has been assigned to. This procedure ensures that the randomization process is not influenced by the healthcare personnel participating in the study. The success of the blinding of the patients will be evaluated at the end of the treatment period.

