#### Recording study data and information on adverse effects

A record will be kept of any side effects experienced, and of possible adverse events arising from either the experimental or the pharmacological treatment.

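### The rule for recording adverse events is inconsistent and partly depends on presumed cause, and the therapist who supplies the data knows the arm, so recording may differ between arms

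*Protocol article*

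**What the plan says.** The protocol article says what goes into the safety record in four places.

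- **Results measures, running text:** "Any adverse effects of the study techniques, and any use of rescue medication by the patient will also be recorded".
- **Treatment, part B (placebo auriculotherapy):** "Any adverse reactions or side effects that may occur will be recorded in the corresponding data logbook, stating details of the reaction, and date of" (the quote stops one word short of the sentence's end). This part also has the placebo arm follow the same protocol as the true arm, "with the application of sticking plaster over inactive black plastic discs".
- **Recording study data and information on adverse effects, single sentence:** "A record will be kept of any side effects experienced, and of possible adverse events arising from either the experimental or the pharmacological treatment".
- **Table 1:** a row labelled only "Adverse events", marked for weeks 1 to 9, under the block "Data provided by the therapist".

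On who knows the arm, the Randomization section says that the healthcare professional "will be informed, both by phone and by fax, which of the two study branches the patient has been assigned to". The Design section claims blinding for patients and analysts only. Safety is named as an aim, next to effectiveness, in the Abstract and the Background.

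**The concern.** An adverse event is normally recorded first and attributed afterwards. Wording that admits only effects of a technique, or events arising from a treatment, puts the causal judgement before the entry. That matters more when the person making the entry knows the arm. A therapist who has applied a disc the protocol calls inactive may be less ready to log an ear complaint as an effect of the technique. Yet both arms wear plaster and follow the same procedure, the eligibility criteria already exclude allergy to sticking plaster, and the Discussion accepts that controls receive stimulation from pressing the implants. Placebo-arm events are therefore plausible.

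The placebo arm is the only reference for safety. If recording differs by arm, the comparison can show a difference that is not there or hide one that is. Blinded analysts cannot repair this, because an event that was never entered is not in their data. Table 1 also lists no patient-reported adverse-event item that could serve as a check.

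**Working it through.** **1. The four statements side by side**

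| Place | What is recorded | Condition on cause | Placebo covered? |
|---|---|---|---|
| Results measures, text | Adverse effects of the study techniques | Yes | Plural wording can cover both arms |
| Treatment, part B | Adverse reactions or side effects | Implied by the terms | Yes, it stands under the placebo heading |
| Recording section, first clause | Any side effects | Implied by the term | No arm named |
| Recording section, second clause | Possible adverse events arising from experimental or pharmacological treatment | Yes | Not named |
| Table 1 | Adverse events | None | Yes, no arm distinction |

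The text and the table give different entry rules. A complaint that the therapist thinks unrelated belongs in the record under Table 1, but not under the Results measures sentence.

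**2. Who applies the rule**

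Table 1 makes the therapist the source, and the Randomization section has the allocation communicated to the treating professional. Together they make the recorder unblinded. The document describes no blinded causality assessment.

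**3. What differential recording would do (assumptions only)**

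The document gives no adverse-event rate and no recording rate, so there is no figure of the plan's own to reproduce on this point. The one input taken from it is 400 patients allocated 1:1, or 400/2 = 200 per arm.

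Let p be the true risk, equal in both arms, and let s_T and s_P be the shares of events recorded in the true and placebo arms.

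- Recorded risks: p × s_T and p × s_P.
- Recorded risk ratio: s_T / s_P, whatever the value of p.
- Chance of a false significant result: power of the two-sided 5% test of two proportions with 200 per arm, by normal approximation (pooled variance under the null, unpooled under the alternative).

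With s_T = 90%:

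| s_P | Recorded risk ratio | Recorded risks at p = 10% | False significance, p = 5% | p = 10% | p = 20% |
|---|---|---|---|---|---|
| 90% | 1.0 | 9% v 9% | nominal 5% | nominal 5% | nominal 5% |
| 70% | 1.29 | 9% v 7% | 7% | 11% | 19% |
| 50% | 1.80 | 9% v 5% | 19% | 35% | 64% |
| 30% | 3.0 | 9% v 3% | 42% | 72% | 96% |

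One cell in full (p = 10%, s_P = 50%): the difference is 0.04. The pooled SE is √(2 × 0.07 × 0.93 / 200) = 0.0255 and the unpooled SE is √((0.09 × 0.91 + 0.05 × 0.95) / 200) = 0.0254. Then (0.04 − 1.96 × 0.0255) / 0.0254 = −0.39, which gives a chance of about 35%.

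Two single datasets show the spread:

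- **Strong filter** (true risk 20%, recording 100% v 50%): 40/200 v 20/200. Pooled risk 0.15, SE = √(0.15 × 0.85 × 2/200) = 0.0357, z = 0.10/0.0357 = 2.80, p about 0.005.
- **Mild filter** (true risk 10%, recording 90% v 60%): 18/200 v 12/200. Pooled risk 0.075, SE = √(0.075 × 0.925 × 2/200) = 0.0263, z = 0.03/0.0263 = 1.14, p about 0.25.

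If the shares are swapped, so that the true arm is under-recorded (70% v 90%), the ratio is 0.7/0.9 = 0.78 and the true treatment looks safer than it is.

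**The case against.** The strongest reply is that placebo-arm events are covered. Table 1 is unqualified. The sentence in Treatment part B stands under the placebo heading and takes in any reaction that may occur, so a plaster reaction under a placebo disc has a place in the logbook. The recording section opens with side effects of any kind, names no arm there, and sets a low threshold by speaking of possible events. This stands. A reader might infer that nothing but treatment-attributed events is recorded, or that a placebo plaster reaction falls outside every rule. The documents do not support either reading.

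The mechanism is also inferred. No section describes an attribution step or says who makes it. No section says that therapists are told the disc is inactive; they are told the arm, and the protocol describes the disc that way. A reader might go on to infer that placebo events will be lost and true auriculopressure made to look less safe. That is one possibility, but therapists trained in the technique could equally under-record in the true arm. Obvious skin reactions under a plaster are also the events least open to causal judgement.

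It can further be said that the article condenses a fuller protocol, that the logbook is not shown, and that no adverse-event test is specified. Missing definitions, forms and tests are therefore not raised here. What remains is that the sentences which are printed disagree with one another, and that the person applying them is unblinded.

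**Conclusion.** The point holds as an inconsistency with a risk of bias, not as a demonstrated bias. The Results measures sentence and the second clause of the recording section make entry depend on a presumed cause, and the terms used in Treatment part B lean the same way. That second clause leaves out the placebo technique. Table 1 sets no such condition. Because the therapist supplies the data and knows the arm, recording may differ between arms wherever the cause-conditional wording is followed.

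Size and direction cannot be determined from the document. Under the assumed values with the true arm recorded at 90%, the recorded risk ratio runs from 1.0 (no distortion) to 3.0. It falls below 1 if under-recording is in the true arm. These figures rest on equal true risks, 200 patients per arm and assumed recording shares, and they are not estimates for this trial. The point still merits a change, because safety is a stated aim, unrecorded events cannot be recovered at analysis, and the correction is cheap.

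**What to change.** 1. Bring the Results measures text, Treatment part B and the recording section into line with Table 1 under one rule: every adverse event in either arm is recorded regardless of suspected cause, and suspected cause is entered later as a separate field.
2. Add one adverse-event item, covering ear or skin and general complaints, to the questionnaire that the blinded patient already completes at T1, and at T2 if wanted. This gives a source that does not pass through the unblinded therapist.
3. Compare the arms on all-cause events, and give events attributed to a treatment as a secondary listing.

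The cost is a change of wording in three places and one item in an existing form. The downside is that more unrelated complaints will be recorded and must be tabulated.

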## Methods

### Design

Randomized controlled multicentre prospective study, with two parallel arms, to compare real auriculotherapy using vaccaria seeds (in accordance with traditional methods and with individual diagnoses) and placebo auriculotherapy. The patients will be blinded to both treatment methods. Analysis of the results will be carried out by professionals who will be blinded with respect to the allocation of patients to the different treatment groups.

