#### Secondary outcome measures

▪ Changes in pain intensity, measured on the 100 mm VAS, at 6 months after beginning treatment.

▪ Changes in the McGill Pain Questionnaire (MPQ), at the end of treatment and after 6 months. The MPQ pain evaluation index consists of 64 pain descriptors divided into 19 subclasses. Within each subclass, the descriptors are classified by intensity.

▪ Satisfaction on the improvement perceived by the patient (PPI) [33], scored by the patient on a 7-point Likert scale as follows: 1 = extremely satisfied; 2 = very satisfied; 3 = moderately satisfied; 4 = no strong feelings either way; 5 = somewhat unsatisfied; 6 = very unsatisfied; 7 = extremely unsatisfied.

▪ Changes in health-related quality of life, according to the Spanish version of the 12-item Short Form health survey, Version 2, at the end of treatment and after 6 months. This questionnaire is of a generic type, derived from SF-36, which has been validated for use in Spain [34], and which enables the quantification of quality of life in 8 dimensions (physical function, physical role, pain, general health, vitality, social function, emotional role, mental health) and expresses two summary components (physical and mental).

▪ Changes in the results of the Lattinen test and in the consumption of analgesics and NSAIDs (whether or not prescribed by the GP), at the time of randomization, after each treatment session, at the end of treatment and after 6 months.

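### The Lattinen test, a secondary outcome, is recorded by therapists who know the allocation, so its post-allocation scores are open to observer bias

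*Protocol article*

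**What the plan says.** - **Outcome status.** The protocol article, Secondary outcome measures, includes "Changes in the results of the Lattinen test and in the consumption of analgesics and NSAIDs", assessed at randomisation, after each session, at the end of treatment and at 6 months.
- **Who records it.** Results measures: "In each treatment session, the therapist will record the five pain-related variables that constitute the Lattinen test (LT". The items are pain intensity, pain frequency, analgesic consumption, activity and sleep. "Each item is scored on a Likert scale from 0 to 4", so the total runs from 0 to 20. Table 1 places the test under "Data provided by the therapist" at T0, weeks 1 to 8, T1 and T2, which is 11 time points.
- **What the recorder knows.** Randomization and treatment allocation: after inclusion the healthcare professional calls and "will be informed, both by phone and by fax, which of the two study branches the patient has been assigned to". The materials also differ to the eye of the person applying them: vaccaria seeds in one arm, "inactive black plastic discs, with a diameter of 1.5 mm" in the other.
- **Who is blinded.** Design: "The patients will be blinded to both treatment methods", and "Analysis of the results will be carried out by professionals who will be blinded with respect to the allocation". No blinded rater is named.
- **What is self-completed.** Results measures has the patient fill in the VAS, the Spanish McGill questionnaire (MPQ-SV) and the SF-12 at T0, T1 and T2.

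**The concern.** All five items depend on what the patient tells the person filling in the form, and that person knows the arm and was trained in the technique under test. A small, consistent lean when choosing between adjacent grades can separate the arms without any treatment effect. Because the lean is already in the recorded data, blinding the analysts does not help.

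Two uses of the test are at stake. First, it is the only pain scale that Table 1 schedules weekly, so any account of the time course of pain would rest on it. Second, secondary goal (i) in the Background compares the characteristics of the Lattinen test with those of the MPQ-SV. One of these is recorded by an unblinded therapist and the other is completed by a blinded patient, so a difference between them cannot be put down to the instruments alone.

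**Working it through.** **1. The plan's own figure.** The only sample size stated is for the VAS. Inputs from Sample size: mean changes of 32.3 and 19.8 mm (difference 12.5 mm), SD 31.9 mm, power 90%, α 5% (taken as two-sided).

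n per group = 2 × (1.960 + 1.282)² × 31.9² / 12.5² ≈ 137, or about 138 with the t distribution. The stated 140 agrees and gives 90.6% power. With 30% dropout, 280 / 0.70 = 400, as stated. Nothing in this point changes that calculation, and the article gives no corresponding figure for the Lattinen test.

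**2. Which ratings are exposed.**

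| Time point | Recorder | Arm known to recorder? |
|---|---|---|
| T0 | Therapist | Unclear: the call follows inclusion, but Secondary outcome measures times the first score only as at randomisation |
| Weeks 1–8 | Therapist | Yes |
| T1, T2 | Therapist | Yes |

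Ten of the 11 ratings follow disclosure. That is enough to expose every change score, even if T0 is clean.

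**3. How large the effect could be.** The documents give no SD for the Lattinen total and no bias size. Both are assumed here, and both are varied.

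- Tilt between arms per item: 0.05, 0.1 or 0.2 point, in the same direction on all five items. On the total this is 0.25, 0.5 or 1.0 point.
- SD of the total: 3 to 5 points.
- Standardised bias b = tilt on total / SD.
- Non-centrality δ = b × √(140/2) = 8.367 × b.
- Chance of p<0.05 with no true effect = Φ(δ − 1.96) + Φ(−δ − 1.96).

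| Tilt per item | Tilt on total | b (SD 5 to SD 3) | δ | Chance of p<0.05 |
|---|---|---|---|---|
| 0.05 | 0.25 | 0.05 to 0.08 | 0.42 to 0.70 | 7% to 11% |
| 0.1 | 0.5 | 0.10 to 0.17 | 0.84 to 1.39 | 13% to 29% |
| 0.2 | 1.0 | 0.20 to 0.33 | 1.67 to 2.79 | 39% to 80% |

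The nominal rate is 5%. More patients make this worse: at 200 per arm, b = 0.1 gives 17% instead of 13%, and b = 0.2 gives 52% instead of 39%.

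**The case against.** The strongest reply is that the article shows an unblinded recorder, not biased scores. It does not say whether the therapist judges the grade or copies down the patient's answer, and analgesic use and sleep are closer to fact than to judgement. This stands: what is shown is a risk, and its size is unknown.

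It can also be said that little rests on this test. No goal in the Background is efficacy on the Lattinen test, and blinded patients supply the VAS at both times, the MPQ-SV, the SF-12 and perceived improvement. A difference seen on the Lattinen test alone would stand out against those. This also stands, and it limits the weight of the point. It does not remove it, because the test is listed as an outcome and no other pain scale is weekly.

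The statement that the randomisation sequence stays concealed does not answer the point, since each patient's arm is disclosed to the rater. Nor does the evaluator mentioned in the exclusion criteria (Subjects), who is not described as separate or blinded, while Table 1 names the therapist.

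A reader might infer more than the documents support, in three ways:
- **That the primary model is contaminated.** Statistical analysis adjusts for baseline pain intensity and frequency but names no instrument. Intensity could be the VAS, and frequency could come from the initial anamnesis. No link to the Lattinen items is established.
- **That the baseline score is taken after disclosure.** The wording is only ambiguous.
- **That false positives are likely.** The upper end of the range needs a tilt of 0.2 point on every item in one direction. The smallest tilt tabulated gives 7% to 11%.

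**Conclusion.** The point holds as a risk of observer bias in a secondary outcome. The text and Table 1 fix the therapist as recorder, the therapist is told the arm, and no blinded rater is named. The Lattinen scores at weeks 1 to 8, T1 and T2 are exposed, and goal (i) is confounded with rater and blinding status. The primary VAS is self-completed by blinded patients and does not pass through this recording route, and the sample size is unaffected.

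The size cannot be fixed from the documents. Under the assumptions above, the chance of a spurious p<0.05 at 140 per arm runs from about 7% to about 80%. A range that wide shows only that a small consistent lean could matter. It is not an estimate of what will happen.

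**What to change.** Have the blinded patient complete the five Lattinen items on paper before each weekly session and at T0, T1 and T2, as the article already does at T0, T1 and T2 for the VAS, MPQ-SV and SF-12. Complete and date the T0 form before the randomisation call. In Table 1, move the test to the patient-provided block and leave auricular points and adverse events with the therapist.

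This needs a form and a table edit, and no extra staff. It has a downside: the mode of administration changes for a test that the article includes because it is widely used in Spanish pain clinics, and the documents do not show that a self-completed form is equivalent. That should be stated when goal (i) is reported. Patients also get a short extra form each week. Self-completion takes the grading away from the unblinded therapist, but it cannot stop that therapist influencing what patients answer, and it relies on patient blinding holding, which the plan checks at the end of treatment.

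If therapist scoring is kept, report the Lattinen test as an unblinded, supportive outcome, base no efficacy claim on it, and still date the T0 score before the call.
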